### Randomization

2.12

After clinical screening and signing the informed consent form, 42 subjects were randomly assigned to the control group and the experimental group according to the proportion of 1:1. This study is an open trial, without blinding, using third-party evaluation and statistics. Each subject will receive different individualized forms of stimulation, while all subjects are aware of the grouping.

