### Interventions

2.7

The intervention measures involved in this study are based on the theory and professional practice knowledge of traditional Chinese medicine. The doctors who are in charge of operating the instruments for treatment have obtained the practicing certificate issued by the national health and Health Commission, and have received more than 3 years of clinical skills training in acupuncture and rTMS. Patients in the experimental group were treated with rMS in M1 area of healthy side, PC6, and SP6 on the affected side, while patients in the control group received acupuncture treatment. In addition, both groups were given basic treatment.

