### Primary outcomes

2.9

NIHSS, score, and simplified fulg Meyer (FMA) score were evaluated before treatment and on day 10. The modified Barthel Index (MBI) was evaluated before and 10 days after treatment and 30 days after treatment

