### Estimation of sample size

2.11

This study is a preliminary clinical study to evaluate the efficacy and mechanism of targeted therapy before, after and during the follow-up period. We plan to enroll 42 participants in this study. (In this study, NIHSS score was used as the effect value. According to the sample size formula of good and bad clinical trials: N = 2δ^2^ × f(α,β)/(u_1_−u_2_)^2^. In the acupuncture group, the NIHSS mean value before treatment was 8.95, the standard deviation was 1.93, and the average NIHSS after treatment was 6.90, sou_1_ = 8.95, u_2_ = 6.90, δ = 1.93, α = 0.05, β = 0.1, f (α, β) = 10.5 from the table, which was substituted into the formula to calculate the sample size n ≈ 19 cases. Considering the loss rate of 10%, the total sample size required was 19 × 2 × (1 + 10%) ≈ 42 cases.)

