### Quality control

2.14

During the whole treatment and follow-up process, patients’ withdrawal and the reasons for withdrawal will be recorded in time. In order to ensure the test quality, the quality supervisor will regularly check all process details and check the authenticity of the data. In addition, the scientific research department of Shaanxi Provincial Hospital of traditional Chinese medicine will be invited to manage the data independently.

Since differences between physicians may lead to bias, each evaluation of the scale will be performed by a designated physician trained in the same evaluation criteria. The 2 physicians in charge of the treatment will receive specialized training in research and operation, including the use of transcranial magnetic stimulation and acupoint localization, prior to recruitment. In order to record treatment compliance, we made a record card for patients, including treatment date, personal information, and signature after each treatment.

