## Discussion

3

Limb dysfunction after stroke is the main complication of stroke and the main cause of adult disability, which seriously affects the working ability and quality of life of stroke patients, and brings serious economic burden to patients and society. With the progress of medical technology, patients have higher expectations of limb function recovery after stroke. Therefore, we designed the clinical research program, hoping to obtain high-quality research data through the improvement of patients’ symptoms and the scale, so as to provide reliable basis for future multicenter research. As a traditional Chinese rehabilitation therapy, acupuncture and moxibustion is widely recognized in the clinical treatment and rehabilitation of stroke. Therefore, we chose the acupuncture program with high public reliability as the control group. PC6 and SP6, as the experimental group, can activate the brain area, increase the link between the brain regions, and strengthen the information exchange between the brain regions. Compared with acupuncture and moxibustion, magnetic stimulation has the advantages of noninvasive, painless, and statistical. In previous clinical trials, it has been confirmed that low-frequency rTMS is of positive significance for the recovery of motor function of stroke patients.^[25]^ However, the use of acupoint magnetic stimulation in the treatment of limb motor dysfunction after stroke is often seen in case reports, and there is no systematic theoretical guidance. The closed-loop rehabilitation theory of “center peripheral center” has great enlightenment on how to improve the treatment effect of limb dysfunction after stroke, but there are few clinical curative effect observation with high confidence based on the “center peripheral center” closed-loop rehabilitation theory. Therefore, based on this theory, we plan to give magnetic stimulation combined with peripheral magnetic stimulation at PC6 and SP6 in central M1 area to observe the effect and difference of acupuncture group on limb function after stroke.

Our scheme is only a pilot study, and its shortcomings include: small sample size, no blindness, short observation time, etc. In the experiment, we will try our best to reduce the error which may affect the research results. Finally, we will prove that rTMS combined with magnetic stimulation of PC6 andSP6 is an effective treatment for limb dysfunction after stroke.

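### The trial is described as wholly unblinded and nothing says the assessor of the three rater-scored primary scales is unaware of the arm, so every primary comparison is open to rater bias that masking could limit

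*Protocol article*

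**What the plan says.** Section 2.12 (Randomization) sets the blinding status: "This study is an open trial, without blinding, using third-party evaluation and statistics". It adds that "all subjects are aware of the grouping".

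Section 2.14 (Quality control) says who scores the scales: "each evaluation of the scale will be performed by a designated physician trained in the same evaluation criteria". The reason given there is that physicians may differ from one another. The two physicians who deliver treatment are described separately in the same section.

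Section 2.9 names three primary outcomes. For the first two: "NIHSS, score, and simplified fulg Meyer (FMA) score were evaluated before treatment and on day 10". For the third: "The modified Barthel Index (MBI) was evaluated before and 10 days after treatment and 30 days after treatment".

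The treatments are visibly different. Section 2.7 gives the experimental group magnetic stimulation, "while patients in the control group received acupuncture treatment". No sham procedure is described.

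The Discussion concedes the point as a limitation: "its shortcomings include: small sample size, no blindness, short observation time, etc".

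**The concern.** NIHSS, Fugl-Meyer and Barthel scores all depend on a rater's judgement. If the rater knows the arm and expects the new treatment to do better, scores can drift in its favour. The analysis cannot separate such a drift from a treatment effect. The same drift could act on all three primary scales, and none of them is an objective measure that would serve as a check. Cortical excitability is only a secondary outcome.

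Patients and operators cannot readily be masked when magnetic stimulation is compared with needling. The outcome assessor can be. The protocol already plans third-party evaluation and a designated scale physician, yet it does not use either to keep knowledge of the arm out of the scoring. The Discussion expects to prove that the combination is effective and hopes to provide a basis for later multicentre research, so a biased estimate would carry forward.

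**Working it through.** **1. What the text says about the assessor's knowledge of the arm**

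| Section | Statement, in summary | Does it address knowledge of the arm? |
|---|---|---|
| 2.12 | Open trial, no blinding | Yes: none, with no exception for assessors |
| 2.12 | Third-party evaluation and statistics | Not stated; the term is not defined |
| 2.12 | Patients know their group | Yes: patients could disclose it to the assessor |
| 2.14 | Designated physician with common training | No: the purpose is consistency between raters |
| Discussion | Lack of blinding listed as a shortcoming | Yes: it confirms the status and adds no safeguard |

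A well-trained, consistent rater who knows the arm can still be consistently biased. Training does not substitute for masking.

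**2. The plan's own sample size**

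Inputs from section 2.11: means 8.95 and 6.90 (difference 2.05), SD 1.93, α = 0.05, β = 0.1, f = 10.5.

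- N per arm = 2 × 1.93² × 10.5 / 2.05² = 18.61, so 19.
- Total = 19 × 2 × 1.10 = 41.8, so 42, or 21 per arm.

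Both figures reproduce. Masking the assessor does not change them.

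**3. Illustration of what a rating shift could do (NIHSS only)**

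Assumptions: no true difference; a systematic between-arm rating shift b, whose values are assumed because the documents give none; a two-sided 5% two-sample t test.

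- Standard error: SE = SD × √(2/n). With SD 1.93 this is 0.626 at n = 19 and 0.596 at n = 21.
- Smallest significant difference: critical t × SE = 2.028 × 0.626 = 1.27 points at n = 19, and 2.021 × 0.596 = 1.20 points at n = 21.
- False-positive rate: probability that |T| exceeds the critical value, where T is noncentral t with 2n − 2 degrees of freedom and noncentrality b/SE. For example, b = 0.5 and n = 21 give 0.5/0.596 = 0.84 and a rate of 13.0%.

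| Assumed shift b | SD 1.93, n = 19 | SD 1.93, n = 21 | SD 2.5 (assumed), n = 19 | SD 2.5 (assumed), n = 21 |
|---|---|---|---|---|
| 0 | 5% | 5% | 5% | 5% |
| 0.25 | 6.8% | 6.9% | 6.0% | 6.2% |
| 0.5 | 12.2% | 13.0% | 9.2% | 9.7% |
| 1.0 | 34.3% | 37.4% | 22.5% | 24.4% |

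The SD of 1.93 is the acupuncture group's pre-treatment value, not a day-10 or change-score SD. The 2.5 columns show how the result moves if the relevant SD is larger. Section 2.13.1 names rank sum or χ² tests for the primary scales, so these t-test figures are not the planned analysis. A change of test does not remove a systematic shift in the scores, but the exact percentages would differ. No figure is offered for Fugl-Meyer or Barthel.

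**The case against.** The strongest reply is that the authors have been open about the limitation, call the work a pilot, and have planned partial protection through third-party evaluation and a designated, trained physician. The published article is condensed, and the full protocol might describe masked assessment. This tempers the severity. It does not settle the point, because the article positively describes the trial as unblinded without excepting the assessor. If masking is intended, that description is wrong and needs correcting.

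Three stronger readings are tempting and are not supported:

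- A reader might infer that the assessor definitely knows the arm, or that third-party means independent but unmasked. The term is never defined. What can be said is that masking is not stated and that the wording suggests there is none.
- A reader might take the percentages as the trial's actual error rate. They rest on assumed shifts, a pre-treatment SD and a t test. At a shift of 0.25 points the inflation is small. Nothing in the documents shows that bias would occur or how large it would be.
- A reader might extend the criticism to cortical excitability and to the statistician. Excitability is a secondary outcome measured with magnetic stimulation, and a masked measurement could need another trained operator. Coding the arms for analysis is commonly left to the statistical analysis plan, which is not shown. Neither is part of this point.

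**Conclusion.** The point holds as a risk in a stated design choice. The trial is declared unblinded, no safeguard is described that keeps the assessor of NIHSS, simplified Fugl-Meyer and modified Barthel unaware of allocation, and these are all of the primary outcomes. Disclosure as a limitation does not reduce the bias.

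The size is unknown. As an illustration under the assumptions above, the nominal 5% error becomes about 7%, 12–13% or 34–37% for shifts of 0.25, 0.5 or 1 NIHSS point at SD 1.93, and about 6%, 9–10% or 22–24% at an assumed SD of 2.5. The design is not invalid, but the bias is largely avoidable and should be addressed.

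**What to change.** In sections 2.12 and 2.14, state that the planned third-party assessor of NIHSS, FMA and MBI takes no part in treatment and is kept unaware of allocation, and say how:

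- assess patients away from the treatment room;
- ask patients not to reveal their treatment;
- withhold the treatment log and the patient record card from the assessor;
- record the assessor's guess of the arm at day 10.

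Replace the statement that there is no blinding with a description of the trial as open-label with masked outcome assessment, and bring the Discussion into line.

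The cost is protocol wording and simple logistics. No additional assessor should be needed for the three scales, provided the designated scale physician is a different person from the two treating physicians, as section 2.14 suggests but does not say outright. The sample size is unaffected. The downside is that some assessors will be unmasked by patient disclosure or visible needle marks. This should be recorded and reported.

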### Statistical analysis

2.13

According to the situation of data collection, data analysis will be based on the principle of intention to treat analysis (ITT) and/or per protocol analysis (PP). We will also evaluate the group effect by comparing the analysis results of the above 2 data sets to evaluate the accuracy of our analysis results.

All data will be analyzed by third-party statisticians using spss23.0 (v23.0, SPSS Inc, Chicago, IL). *P* < .05 was significant. Descriptive statistics will be carried out by group and time for average, standard deviation, maximum value, minimum value, and so on.

The data of the patients were collected and summarized. The quantitative indexes were *t* test and rank sum test. *χ*^2^ test (ANOVA) was used for non-rank counting, and rank sum test was used for grade counting. All statistical tests were performed with bilateral test. If *P* value is less than or equal to .05, the difference will be considered statistically significant.

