#### Withdrawal criteria

2.3.3

1.After inclusion, it was found that they were not suitable to continue to participate in the study.2.Those who fail to treat according to the regulations affect the evaluation of curative effect.3.Withdrawal of consent by the subject or a legal representative.4.Loss to follow-up.5.Serious adverse events.6.Significant errors or deviations were found in the clinical protocol.7.New infarct or secondary hemorrhage occurred and the condition deteriorated.

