#### Adverse reactions and countermeasures of magnetic stimulation

2.8.1

Magnetic stimulation may induce epilepsy, local skin numbness, pain and discomfort, and other adverse reactions. In the treatment process, the intensity, frequency, and stimulation times can be changed according to the patient's condition to reduce the occurrence of adverse reactions.^[21–23]^ During the study, a patient treatment log will be established to monitor all adverse reactions during treatment and follow-up, and appropriate intervention will be carried out. If serious adverse reactions occur during the treatment, they should be reported to the principal investigator immediately, and the details should be recorded in the patient's treatment log and corresponding treatment measures should be taken, such as adjusting the coil position and stimulation intensity to avoid stimulating the sensitive orbitofrontal cortex (100% RMT → 80% RMT), or giving appropriate medical intervention according to the patient's condition. If the subject or researcher thinks that the patient cannot tolerate these adverse reactions, the trial can be terminated and the subject will withdraw from the study.

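### The analysis set is left as ITT and/or PP, depending on how data collection goes, with neither primary, while the withdrawal criteria include reasons tied to treatment and outcome

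*Protocol article*

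**What the plan says.** Section 2.13 (Statistical analysis) of the protocol article sets the analysis population in one sentence: "According to the situation of data collection, data analysis will be based on the principle of intention to treat analysis (ITT) and/or" per-protocol analysis. It then proposes "comparing the analysis results of the above 2 data sets to evaluate the accuracy of our analysis results". No set is called primary, and nothing says which one decides the conclusion if they disagree.

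Section 2.3.3 (Withdrawal criteria) lists reasons for withdrawal after inclusion. Among them are:

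- "After inclusion, it was found that they were not suitable to continue to participate in the study"
- "Those who fail to treat according to the regulations affect the evaluation of curative effect"
- "Serious adverse events"
- "New infarct or secondary hemorrhage occurred and the condition deteriorated"

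Section 2.8.1 says of a patient who cannot tolerate adverse reactions to magnetic stimulation that "the trial can be terminated and the subject will withdraw from the study". Section 2.8.2 says the same for acupuncture.

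Section 2.9 schedules NIHSS and FMA at baseline and day 10, and MBI at baseline, day 10 and day 30. Section 2.12 describes an open trial with third-party evaluation and statistics, and 2.14 says that withdrawals and their reasons are recorded.

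**The concern.** A protocol may leave the definition of analysis sets to a statistical analysis plan. This one does not leave the matter open. It states a rule, and the rule lets the course of data collection decide. Read as written, it permits a PP-only result, or a choice made late in an open trial.

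That matters more because of who can leave the PP set. Non-adherence, serious adverse events and neurological deterioration are not random. Deterioration is close to what NIHSS, FMA and MBI measure. The expected adverse reactions also differ by arm: seizure, numbness and pain with stimulation; fainting, needle problems and haematoma with acupuncture. Exclusions on these grounds can differ between arms, and a comparison without those patients is no longer protected by randomisation. The same holds for an analysis labelled ITT if these patients have no scores.

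Two things are at stake: a type I error above the nominal 5% from having two sets to choose between, and a biased difference if poor outcomes are lost unequally.

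**Working it through.** **Inputs.** 21 per arm (2.5). NIHSS means 8.95 and 6.90, SD 1.93, α = 0.05, β = 0.1, f(α,β) = 10.5, loss 10% (2.11). Two-sided tests (2.13).

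**The plan's own figure.** 2 × 1.93² × 10.5 / (8.95 − 6.90)² = 78.22 / 4.2025 = 18.61, rounded up to 19 per arm. Then 19 × 2 × 1.10 = 41.8, rounded up to 42. The stated sample size reproduces and is not in dispute here.

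**What the planned loss means.** 10% of 21 is 2.1, about two per arm; 10% of 42 is 4.2, about four in all.

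**Illustration.** The documents give no loss pattern by arm, so three patterns are assumed. Each was simulated with 40,000 trials, no true effect, normal outcomes with SD 1.93, 21 per arm, and a two-sided t test with p ≤ 0.05. With all patients analysed the type I error is 0.0495. The simulation error is small: at 0.065 the standard error is √(0.065 × 0.935 / 40,000) ≈ 0.001.

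The reduced set is PP, or ITT without the withdrawn patients' scores. The last column takes whichever of the full ITT set and the reduced set is significant, so it assumes that full ITT scores exist.

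| Patients lost | Number | Mean shift (NIHSS points) | Type I error, reduced set | Type I error, either set |
|---|---|---|---|---|
| At random, each arm | 1 | none | 0.050 | 0.060 |
| | 2 | none | 0.050 | 0.065 |
| | 3 | none | 0.051 | 0.068 |
| | 4 | none | 0.051 | 0.072 |
| Worst scores, experimental arm only | 1 | 0.19 | 0.069 | 0.079 |
| | 2 | 0.34 | 0.100 | 0.116 |
| | 3 | 0.49 | 0.144 | 0.164 |
| | 4 | 0.62 | 0.196 | 0.218 |
| Worst scores, each arm | 1 | none | 0.065 | 0.066 |
| | 2 | none | 0.078 | 0.079 |
| | 3 | none | 0.088 | 0.090 |
| | 4 | none | 0.097 | 0.100 |

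Section 2.13.1 names the rank sum test among the tests for the primary outcomes. In 20,000 simulated trials with that test, losing the two worst scores gives about 0.09 (one arm only) and about 0.074 (both arms).

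**Reading the table at the planned loss of about two per arm.**

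- The free choice of set, taken alone, raises the type I error from 5% to about 6.5%.
- If the two worst scores were lost from one arm only, the difference would move by 0.34 points, or 0.343 / 2.05 ≈ 17% of the difference used for sample size, with a type I error of about 9–10%.
- If the two worst were lost from both arms, there would be no mean shift. The type I error would be about 7–8%, because cutting one tail shrinks the within-arm variance that the test uses.

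**The case against.** Four points can be made for the plan.

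**Withdrawn patients may still be assessed.** A reader might infer that their day-10 and day-30 scores are not collected, so that even ITT must omit them. The documents do not say so. Section 2.3.3 only lists criteria. Sections 2.8.1 and 2.8.2 speak of leaving the study, which suggests an end to assessment but does not state it. A condensed article may also leave assessment after withdrawal and missing-data methods to a fuller document. This objection stands: loss of the worst outcomes is possible, not established.

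**The choice may not depend on results.** A reader might infer that the set is picked after outcomes by arm have been inspected. The wording can equally refer to how complete the data are. Both sets are to be compared, which implies that both are run, and third-party statisticians do the analysis. These points lessen the risk of selective reporting. They do not remove it, since the rule still permits one set alone and gives neither priority.

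**The larger figures are not forecasts.** A reader might take 10% or 14% as the expected type I error. Those figures assume that the two or three worst scores leave one arm and none leave the other, which nothing in the documents supports. The figure that measures the and/or rule itself, at the planned loss, is about 1.5 percentage points above nominal.

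**Comparing the sets is useful.** If ITT keeps the withdrawn patients, ITT and PP differ in exactly those patients, and the comparison is an ordinary sensitivity check. Only the claim that it shows accuracy goes too far.

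The article also calls the trial preliminary and a pilot. That lowers the stakes but does not justify an undefined primary population in a plan that expects to demonstrate efficacy.

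**Conclusion.** The point holds in a limited form and should be fixed. What is established is that 2.13 makes the analysis set depend on data collection and names neither ITT nor PP as primary, while 2.3.3 lists withdrawal reasons related to treatment or outcome. A PP result, or an ITT result without those patients' scores, could therefore be biased. Whether withdrawn patients are still assessed is not stated, so the bias is a risk whose direction and size cannot be read from the documents.

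The cost of the undefined choice at the planned loss is modest. The larger figures show how far a selective loss could carry the result and should be quoted only with their assumptions: no true effect, normal scores, 21 per arm, SD 1.93 and an invented loss pattern.

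**What to change.** **In 2.13**, replace the and/or sentence with, for example: *The primary analysis includes all randomised patients in the arm assigned (ITT); PP is a sensitivity analysis and cannot replace it.* Keep the comparison of the two sets, but describe it as a sensitivity check and not as evidence of accuracy.

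**In 2.3.3**, leave the rules on stopping treatment as they are, and add that stopping treatment does not end assessment: NIHSS, FMA and MBI are still taken at day 10, and MBI at day 30, as already scheduled, unless the patient withdraws consent for follow-up. This adds no assessment beyond the existing schedule.

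**Optional:** a worst-rank sensitivity analysis for patients who cannot be assessed because of deterioration or death.

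**Cost:** a few sentences, the already planned visits for about four patients, and possibly a slightly smaller estimate under ITT. The sample size does not change. The assessment wording is best added early, because scores not taken on schedule cannot be recovered later.
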